### Sample size

To achieve our study objectives, the sample size calculation estimates 405 participants. With a significance level set at 5% (i.e. overall type-I error probability) and power of 80%, an assumed rate of falls of 0.5 for the T&E program, 0.79 for the OTAGO and 0.92 for the usual care group, a non-inferiority margin of 5% and an assumed dropout rate of 15%, we would need to include 162 participants in the groups A and B each, and 81 participants in the group C. We used the R package “ThreeArmedTrials” to calculate the sample size [83].

The allocation scheme of 2:2:1 is based on ethical and statistical considerations, following the recommendations of Mütze et al. [84] and Mielke et al. [85].

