### Statistical analysis

Descriptive statistics will be used to present group characteristics on age, sex, body mass index, base of support width (BSW) [86, 87], and history of falls, activity of daily live, physical activity habits, and risk factors for falls.

According to statistical criteria of termination of the trial, we have no predefined stopping rules because we are not expecting risks that are different in the groups (i.e. no adverse event stopping criteria).

We will use an intention-to-treat analysis based on all randomized patients, with missing values and dropouts replaced by multiple imputation methods, as recommended by current guidelines on randomized controlled trials [88].

The primary analysis will be done to test for the incidence of falls. We follow the proposition of Röhmel and Pigeot [89], who showed that superiority of the experimental group (“T&E” in our case) over the reference treatment (“Otago” in our case) can be tested after successfully demonstrating non-inferiority (if stated a-priori in the protocol). To simultaneously demonstrate superiority of E (T&E) to R (Otago) and R (Otago) to P(Helsana) as well as the non-inferiority of E (T&E) to R (Otago), we will use negative binomial regression [90, 91] and follow an approach proposed by Mütze et al. [84]. A sensitivity analysis without multiple imputations of missing values will be performed.

For the primary analyses, we will adjust for the participants’ length of observation, center, age and risk for falls category [92]. We will perform a per protocol sensitivity analysis including time varying co-variables to reduce confounding and selection bias, e.g. due to differential censoring.

Further analyses will be performed to test the secondary endpoints quality of life (Overall score of OPQOL-35), severity of falls (Schwenk Scale), fear of falling (FES-I), functional capacities (TUG, FSBT, FTSTS, FR and SMWT), as well as adherence to the exercise recommendations (duration in min/week, frequencies/week).

We will perform a subgroup analysis based on age groups to test the secondary hypothesis that compliance in older group is better with the Otago compared to T&E and that in younger participants’ compliance is better in T&E compared to Otago.

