The data monitoring committee will do interim analyses only for data quality evaluation and for monitoring of adverse events, i.e. no interim for effectiveness will be performed. The results of this analyses will be accessible for the steering committee.

The proportion of adverse events (other than falls) will be compared between the groups by an external and independent statistician.

All deviations from the statistical plan will be documented and an amendment will be sent to the ethical commissions as well as to Protocol Registration System ClinicalTrials.gov. The deviations from plan to actual analysis will also be reported in the final publication(s).

We will use multiple imputation methods using 50 imputed datasets under the assumption that missing data are missing at random. We will run sensitivity analyses to test the robustness of our replacement models and the robustness of the assumption “missing at random”.

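### Non-fall adverse events are compared as a proportion, which allows for neither unequal follow-up nor recurrence; a rate per person-year should be added

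*Protocol article*

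**What the plan says.** All of the following is in the protocol article.

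- **Harms (Statistical analysis).** One sentence covers the comparison: "The proportion of adverse events (other than falls) will be compared between the groups by an external and independent statistician". It gives no denominator, model or handling of follow-up time.
- **Falls (Statistical analysis).** Falls are analysed by negative binomial regression, and "For the primary analyses, we will adjust for the participants’ length of observation, center, age and risk for falls category". The adjustment is stated for the primary analyses only.
- **Unequal loss (Statistical analysis).** The section plans a "per protocol sensitivity analysis including time varying co-variables to reduce confounding and selection bias, e.g. due to differential censoring".
- **Dropout (Sample size).** The calculation uses "an assumed dropout rate of 15" per cent, as one figure for the whole trial. Planned arm sizes are 162, 162 and 81.
- **Types of event (Adverse events).** The list includes worsening of existing illness and more frequent or more intense episodic conditions. Events reach the local investigator when the patient, family, a caregiver or the physiotherapist notices and reports them.

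**The concern.** An adverse event can be recorded only while someone is in a position to report it. In a proportion, a participant who leaves event-free in month 2 counts the same as one followed event-free for twelve months. If one arm loses more participants, its recorded proportion falls even when the true event rates are equal, and the error is in the reassuring direction for that arm.

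The measure also fits the listed events poorly, because an exacerbation can recur. If the proportion is of participants, repeat events are dropped. If events are counted in the numerator, the result is not a proportion, and it still depends on how long each arm was observed.

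This is the only between-group comparison of non-fall harm that the article describes. The plan already deals with observation time for its other event outcome, falls, so the two are treated inconsistently.

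**Working it through.** The plan gives no figure for the adverse event analysis, so there is nothing to reproduce. The check asks how far a proportion moves when only dropout differs.

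**Inputs from the article:** 15% overall dropout and 162 per arm for T&E and Otago (Sample size); twelve months of participation (Patient flow).

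**Assumptions, not in the article:** the same true event rate h in both arms (0.1, 0.3 or 0.6 per person-year); dropout of 20% versus 10%, or 25% versus 5%, each averaging 15% over two equal arms; dropout times spread evenly over the year; constant hazard; event capture ending at dropout.

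**Step 1: proportion with at least one event.** For completers it is 1 − exp(−h). For dropouts it is 1 − (1 − exp(−h))/h. With dropout fraction d:

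P(d) = (1 − d)(1 − exp(−h)) + d[1 − (1 − exp(−h))/h]

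At h = 0.3 the two parts are 0.2592 and 0.1361.

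- d = 0.25: 0.75 × 0.2592 + 0.25 × 0.1361 = 0.228
- d = 0.05: 0.95 × 0.2592 + 0.05 × 0.1361 = 0.253, so the ratio is 0.90
- d = 0.20 gives 0.235 and d = 0.10 gives 0.247, so the ratio is 0.95

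| h per person-year | Ratio, 20% vs 10% | Ratio, 25% vs 5% |
|---|---|---|
| 0.1 | 0.948 | 0.899 |
| 0.3 | 0.950 | 0.903 |
| 0.6 | 0.953 | 0.908 |

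With equal dropout the ratio is 1.00.

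**Step 2: size against sampling error.** At h = 0.3 and 25% versus 5%, the gap is 2.5 percentage points. The standard error is √[(0.228 × 0.772 + 0.253 × 0.747)/162] = 0.047, so the gap is about half a standard error. At 20% versus 10% it is 1.2 points.

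**Step 3: a different dropout model.** Take exponential dropout and a true 12-month risk of 30%, so h = −ln 0.70 = 0.357 and c = −ln(1 − d). The proportion is h/(h + c) × [1 − exp(−(h + c))].

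- 10% versus 20% dropout: 28.6% versus 27.1%, ratio 0.95. A nominal 5% two-sided test has about 6% error.
- 5% versus 25% dropout: 29.3% versus 26.3%, ratio 0.90, error about 9%.
- If every dropout left at month 3, the gaps would be 2.1 and 4.3 points.

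**Step 4: rate per person-year.** Under the Step 1 assumptions, expected follow-up is 1 − d/2 years and expected events are h(1 − d/2). At h = 0.3, 25% dropout gives 0.2625/0.875 = 0.30 and 5% gives 0.2925/0.975 = 0.30, so the rate ratio is 1.00. Events per randomised participant, by contrast, give 0.2625/0.2925 = 0.90.

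**Step 5: where the rate fails.** Suppose reporting runs at 2r in the first six months and r in the second.

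- A completer has 1.5r expected events in one year.
- A dropout has 2r × 0.375 + r × 0.125 = 0.875r expected events in half a year on average.
- At 25% dropout: (0.75 × 1.5 + 0.25 × 0.875)r/0.875 = 1.536r.
- At 5% dropout: (0.95 × 1.5 + 0.05 × 0.875)r/0.975 = 1.506r.
- The ratio is 1.02, a small bias in the opposite direction.

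**The case against.** The strongest reply is that one sentence in a condensed article does not fix a crude analysis. The denominator, model and handling of recurrent events are commonly left to a fuller plan, and a proportion of participants with an event is a standard safety summary. This stands in part. A reader might infer that the plan commits to an unadjusted test, but the article does not say so. It does name a proportion as the measure, and it states adjustment for observation time only for the primary analyses.

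Second, the Statistical analysis section promises intention-to-treat with multiple imputation for dropouts, and under Outcomes those who stop are asked to attend later assessments, so capture need not end at dropout. This also stands in part, since neither provision clearly reaches these events. What the article says will be asked about at those assessments is falls. With spontaneous reporting, an unreported event looks like no event rather than a missing value.

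Third, a reader might infer that the authors expect unequal losses. The article does not support this. The phrase "to reduce confounding and selection bias, e.g. due to differential censoring" is an example attached to a per-protocol sensitivity analysis, and the sample size uses one dropout rate. Unequal loss is plausible, because T&E and Otago have eight sessions and four calls while Helsana has one session and four calls, but it is not forecast.

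Fourth, harms are not otherwise unwatched. Falls are the primary outcome and are adjusted for observation time, fall severity is analysed, and the data monitoring committee monitors adverse events. That limits what is at stake.

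**Conclusion.** The point holds as a minor one. The named measure suits neither unequal follow-up nor recurrent events, and it is out of line with the handling of falls. If losses differ between arms, the ratio of proportions is about 0.95 at 20% versus 10% dropout and 0.90 at 25% versus 5%, whichever of the assumed event rates is used. That is about half a standard error or less at h = 0.3, and more if losses come early or events are common.

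It would go too far to conclude that the worse-retained arm will look safer in this trial. That needs unequal loss, similar true rates and capture that stops at dropout, and the article establishes none of these. Nor is a person-year rate exact: it returns 1.00 only under constant hazard and non-informative dropout.

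**What to change.** Keep the number and proportion of participants with at least one adverse event other than falls, with the denominator stated. Add adverse events other than falls per person-year of observation. Compare the groups with a negative binomial model, or Poisson with robust standard errors if events are sparse, using log observed time as offset. State when observation for adverse events ends, since it may outlast the diaries in participants who stop but still attend assessments. Settle the wording before any group comparison is seen.

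The cost is a sentence or two in the analysis section and one more model for the external statistician; length of observation is already needed for the falls model. The rate does not cure informative dropout, a hazard that changes over the year, or differences in reporting that come from the different contact intensity between arms. It should be read beside the proportion, not instead of it.

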Home-based exercise programmes appear to reduce rate of falls [33], number of fallers, risk factors for falls, and risk of death [34] by improving balance, leg strength, function, physical activity [35] and balance confidence in older adults living in the community [36].

To maintain the effects of the home-based exercise programmes, older people should continue as long as possible with these exercises. However, older adult’s adherence to exercise interventions declines over time [37, 38]. A variety of factors determine, increase or decrease adherence to exercise in older adults [39]. These factors could be psychological and cognitive, behavioural, physical or simply organisational. The strongest motivator affecting exercise adherence in older adults is *self-efficacy* [39] and the integration of the *self-efficacy* concept in exercise programmes to enable individuals to continue with the programme is highly recommended [37, 40].

Because *self-efficacy* is a modifiable factor, project promoters and researchers could enhance the adherence in falls-prevention interventions using specific recommendations [41]. There also is a range of factors affecting the implementation of fall-prevention practices. They are related to older adults, families, healthcare professionals and healthcare systems [42]. General considerations consist in raising awareness in the population and in health professionals [7, 43], promotion of benefits of exercises in older people [43, 44] and consideration of the individual lifestyle, values and capabilities [7, 43, 44]. More specific, encouraging confidence in self-management by giving older adults an active role [43] and providing moderate follow-up visits [7, 45] could improve adherence to home exercise programmes for prevention of falls. Currently, with the advent of e-technology, several studies use mobile applications [46–49] to improve adherence and motivate older adults living in their own home to exercise. Therefore, we developed a new home-based exercise programme, based on the concepts of self-efficacy and of empowerment, delivered on a mobile application. Because older people have to test the exercises before starting to train, this programme is named Test and Exercise (T&E).

The aim of this study is to compare the effects of the T&E exercise programme with the effects of the Otago and Helsana exercise programmes in older adults at-risk for falling, while living in their own home.

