### Outcomes

The primary outcome “falls incidence” and exercise frequency will be assessed prospectively and for twelve months with self-recorded monthly diaries. If a patient decides to stop his participation (completing monthly diaries and exercise training), the physiotherapist will ask him to participate at the intermediary or/and finale assessment. Physiotherapist-assessors who are unaware of group allocation (“blinded assessors”) will assess the secondary outcomes at baseline, at the six-month intermediary assessment, and at the twelve-month final assessment. All assessors are independent physiotherapists and specially trained to perform the assessments.

To ensure that the assessors remain unaware of the group allocation, patients are told not to talk about their treatment with the assessor.

The main outcome is the incidence of falls for twelve months. For this study we define a fall as “*an unexpected event in which the participant comes to rest on the ground, floor, or lower level, with or without injury*” as recommended in the systematic review of Hauer et al. [59]. The history of falls (number, circumstance (Where? *Inside OR outside;* When? *Day OR night;* How? *Describe shortly the event*) and severity) in the previous twelve months will be assessed at baseline. During the study, falls will be prospectively self-reported (number, date, circumstance and severity) in monthly diaries [60]. To ensure that the patients complete the diaries, the physiotherapists will check them at each visit and ask about the diaries during each phone call [59]. In addition, falls events (number, circumstance and severity) will be asked during the intermediary assessment and at the final assessment. The diaries will be sent to the coordinators. The coordinators will send them in PDF version to the project-assistant. She will enter the data in REDCap software once a month.

Secondary outcomes include severity of falls, fear of falling, gait, strength and balance and quality of life. They will be assessed at baseline, at the intermediary assessment and at the final assessment. They also include exercise-adherence. This outcome will be assessed at twelve months.

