
Quality of life will be measured with the French and German version of the “Older People’s Quality of Life Questionnaire” OPQOL-35 [82]. The questionnaire consists of 35 items measuring quality of life based related to eight domains: 1: Life overall (4Q), 2: Health (4Q), 3. Social relationships (8Q), 4: independence, control over life, freedom (5Q), 5: home and neighbourhood (4Q), 6: Psychological and emotional well-being (4Q), 7: Financial circumstances (4Q) and 8: Culture and religion (2Q). The score ranges from 35 to 175: as higher the score, as better the quality of life.

Adherence to exercise will be prospectively assessed in monthly training diaries during 12 months where date, duration, type of exercises (including walking) and intensity of effort are noted. To ensure that the patients complete the diaries, the physiotherapists will check them at each visit and ask about the diaries during each phone call.

Confounding factors, like life situation, living place, physical activity habits and comorbidity will be documented at each assessment session.

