## Discussion

### Strengths

Because of the growing older population, physiotherapists will be more and more requested for intermediate care services including home-based models [93]. In this multicentre study we built a network with engaged health providers in vulnerable community dwelling older people. In this cross-disciplinary model, physiotherapists taking care of patients at their own home will bring their competences to improve function, independence and quality of life in this population.

In addition, this RCT evaluates the effects of three structured home-based exercise programmes of which two are implemented by physiotherapists. We expect larger reduction on the incidence of falls in these two programmes, indicating the efficient role of the physiotherapists with the patients. Because the T&E programme is person-centred and based on self-efficacy and empowerment, we expect a larger effect of T&E on quality of life and on exercise-adherence.

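### As written, missing-at-random imputation also covers the adherence of people who stopped exercising, which overstates mean adherence and distorts the comparison between programmes

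*Protocol article*

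**What the plan says.** The Statistical analysis section of the protocol article plans an intention-to-treat analysis of all randomised patients, "with missing values and dropouts replaced by multiple imputation methods". Later in the same section it adds: "We will use multiple imputation methods using 50 imputed datasets under the assumption that missing data are missing at random". Neither sentence is confined to falls, and neither excepts an outcome. The next sentence promises sensitivity analyses of the imputation models and of the missing-at-random assumption, without describing them. An analysis without imputation is also planned, but it is stated in the paragraph on the primary falls analysis.

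Adherence is listed among the secondary endpoints as "adherence to the exercise recommendations (duration in min/week, frequencies/week"). Its source is given under Outcomes: "Adherence to exercise will be prospectively assessed in monthly training diaries during 12 months". The diaries also record walking.

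Outcomes also says what leaving involves: "If a patient decides to stop his participation (completing monthly diaries and exercise training"). Such a person is invited to the later assessments. No rule says how the diary months after leaving are counted for adherence.

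**The concern.** For most outcomes, a person who leaves has an unobserved value that others may help to predict. Adherence is different. If one decision ends both the diary and the training, the reason the diary is blank is the behaviour being measured. Under missing at random, people who left are treated as exercising like people with a similar observed record who stayed. Nothing in the continuers' data can tell the model that the leavers stopped.

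Adherence is secondary, but it is in the article's title, and under Strengths the authors write that "we expect a larger effect of T&E on quality of life and on exercise-adherence". An age-subgroup hypothesis compares compliance between T&E and Otago. The Background states that "older adult’s adherence to exercise interventions declines over time", so stopping is an expected process. Stopping could also differ between programmes: T&E and Otago have eight sessions and four calls, Helsana one session and four calls.

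**Working it through.** **Inputs from the article.** The Sample size section gives "an assumed dropout rate of 15"% for the trial as a whole and 162, 162 and 81 participants per group. 162 + 162 + 81 = 405, and 0.15 × 405 = 60.75, so about 61 people are expected to drop out. The article states no adherence level, no dropout by group and no time of stopping, so there is no adherence figure to reproduce.

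**Assumed inputs.** Continuers exercise m min/week, a proportion d stop, and stoppers do no programme exercise afterwards. The values of m, the values of d by group and the time of stopping are illustrations.

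**Step 1: level, simple imputation within programme.**
- Mean with stopped time counted as zero: m(1 − d) if stopping is from the start, m(1 − d/2) if at half-time.
- Mean under imputation that treats stoppers like continuers: m.
- With m = 90 and d = 0.15 from the start: 90 × 0.85 = 76.5 against 90. Ratio 1/0.85 = 1.18.
- With stopping at half-time: 90 × 0.925 = 83.25 against 90. Ratio 1.08.

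**Step 2: difference between two programmes (min/week).**

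| Continuers | Stopping | Difference, stop from start | Difference, stop at half-time | Difference under imputation |
|---|---|---|---|---|
| 90 vs 90 | 10% vs 20% | 81 − 72 = 9.0 | 85.5 − 81.0 = 4.5 | 0 |
| 90 vs 90 | 5% vs 25% | 85.5 − 67.5 = 18.0 | 87.75 − 78.75 = 9.0 | 0 |
| 100 vs 80 | 15% vs 15% | 85 − 68 = 17.0 | 92.5 − 74.0 = 18.5 | 20 |
| 90 vs 90 | 15% vs 15% | 0 | 0 | 0 |

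With unequal stopping and equal continuers, the difference disappears. With equal stopping and unequal continuers, the absolute difference is enlarged, while the ratio is unchanged (85/68 = 100/80 = 1.25). With both equal, only the level is wrong.

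**Step 3: does a better imputation model cure it?** A simulation (200,000 people per setting) let the imputation use each person's earlier diaries. First-half exercise had mean 90 and SD 30 min/week. Second-half exercise was 0.9 times the first-half value plus noise of SD 20. Low exercisers stopped more often, and stoppers' true second-half value was set to zero. Stoppers were filled in with the regression prediction fitted in continuers, which multiple imputation reproduces on average. Second-half means in min/week:

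| Stopping | True mean | Imputed mean | Ratio | Mean value given to stoppers |
|---|---|---|---|---|
| 10% | 75.0 | 80.9 | 1.08 | 59.3 |
| 15% | 71.9 | 81.1 | 1.13 | 61.1 |
| 20% | 68.6 | 81.1 | 1.18 | 62.6 |

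Earlier diaries lower the values given to stoppers, but leave them far from zero.

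**The case against.** The strongest reply has five parts.

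1. *The imputation sentences do not name adherence, and the full analysis plan, not shown, may treat it separately.* That may be so. But the article does more than leave a detail open: it states a general rule that, read plainly, includes adherence.

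2. *Zero is not known.* This stands. A reader might infer from the Outcomes section that exercise after leaving is an established zero. The bracketed words only explain what participation covers. The programmes are home-based, Helsana is self-directed, and the diaries include walking, so some people may continue unrecorded. Zero programme exercise is an assumption, though a more plausible one for a documented stop than the level of people who continued.

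3. *The plan already tests missing at random.* It does, and a reader should not conclude that the assumption goes unchallenged. But the tests are undescribed, and the main adherence estimate stays as it is whatever they show. The analysis without imputation is placed with falls and, applied to adherence, would also leave out the stopped months.

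4. *Few people are affected.* This partly stands. Someone who stops exercising but keeps the diary has observed zeros. Someone who stops only the diary may still exercise, and imputing that person is reasonable. The point concerns those who stop both.

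5. *Diaries are dated, so the last session can be derived.* The last recorded session does not show whether the exercise stopped or only the diary.

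**Conclusion.** The point holds in a limited form. As written, the general imputation rule gives people who stopped training adherence values modelled on people who continued. If their programme exercise is at or near zero, mean adherence is overstated, by up to about 18% at 15% stopping from the start. The figure is about 8% if stopping is at half-time and imputation is simple. With earlier diaries as predictors it is about 13% for the second half-year alone. All these sizes rest on assumed exercise levels and times of stopping; only the 15% comes from the article, and there it is an overall dropout rate.

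It is tempting to say that the rule always hides differences between programmes. The documents do not support that, because they give no stopping rates by group. A difference is hidden when stopping rates differ and continuers are alike; the absolute difference is enlarged when stopping is equal and continuers differ. Distortion is the accurate word.

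The outcome is secondary and the primary falls analysis is not affected, so this should be corrected but does not threaten the trial's main conclusion.

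**What to change.** State in the analysis section that, for the main analysis of minutes and sessions per week:

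- months after a documented stop of exercise count as zero programme exercise, with walking or other exercise counted only if recorded;
- multiple imputation is used only for diaries missing for other reasons;
- the missing-at-random version is kept as a sensitivity analysis.

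Record whether and when exercise was stopped, separately from when the diary was stopped.

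The cost is a short addition to the text and one added data item (exercise stopped or not, with the date). Reported adherence will be somewhat lower, and zero will be wrong for anyone who continues some exercise without recording it. The sensitivity analysis shows how far the result depends on that choice.
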